**Figure 3 Fig3:**
[figure not shown]
**The main procedure for the measurement of diffuse noxious inhibitory controls (DNIC) function. A.** On the Ashi-point of the knee, a 180-g von Frey filament is used to prick three to five times within a 1-cm-diameter circle at an angle of 45-degrees between the filament and the skin. The patients will be asked to rate the intensity of pain as VAS1. **B.**The patients will be asked to immerse the contralateral hand, including the wrist, into nociceptive cold water (10 to 12°C) for 1 minute, and the doctors will rate the intensity of the 180-g von Frey filament-induced pain at the Ashi-point as VAS2. DNIC = (VAS1-VAS2)/VAS1.

WOMAC can be used as an initial assessment of the intensity of pain and functional disability of KOA [3]. It is a multidimensional measure of pain, stiffness, and physical functional disability [17]. Briefly, five questions will be asked about pain dimension at activity or rest. The stiffness dimension includes two questions. Questions about the degree of difficulty in 17 different activities will be asked for the physical functional disability dimension. All 24 questions will be listed in a numerical rating scale ranging from 0 (no symptoms) to 3 (maximum symptoms). Doctors need to help patients perform the self-assessment, collect the total score from the 24 questions and record it.

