**Trial flow chart.**

### Randomization and blinding

Patients who meet the inclusion criteria will be randomly assigned to one of three groups (strong EA, weak EA or sham EA) in a ratio of 1:1:1 using a computer-generated random allocation sequence through the stratified block randomization method of SAS version 9.1.3 (SAS Institute Inc., USA). The randomization will be performed by an independent research assistant, who will inform the acupuncturists of the treatment assignments by mobile message. Allocation concealment will not be exposed until the final data analysis report is completed.

To maintain blinding, each patient will have needles (true or sham) inserted into his/her ipsilateral leg. The needles are connected to an EA apparatus, and the patients can feel electric stimulation. Strong and weak EA groups will be acupunctured on four acupoints. The sham EA group will be acupunctured on four non-acupoints without ‘De-qi’.

In this clinical trial process, the patients, statisticians and the evaluators for the statistical data and outcomes are blind to the treatment allocation. However, the blind method is not used by acupuncturists in the implementation of EA manipulation because it is not feasible to conceal allocation from them.

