**Figure 2 Fig2:**
[figure not shown]
**The points used in the trial.** The lines refer to acupoints of ‘Liangqiu’ (ST34) and ‘Dubi’ (ST35) on the lateral side of the knee, and ‘Xuehai’ (SP10) and ‘Neixiyan’ (EX-LE5) on the medial side of the knee. The points lateral to the above four acupoints refer to non-acupoints.

After the local area has been disinfected, the needles (30-gauge with an outer diameter of 0.32 mm and a length of 50 mm) will be inserted at a depth of 25 to 40 mm vertically and ‘De-qi’ (the acupuncture sensation of fullness, heaviness, dull aching or warmth) sensation will be achieved in the strong and weak EA groups through lifting and thrusting combined with twirling and rotating the needles. Direct current and continuous wave will be delivered with a medical EA apparatus (model G9805, Shanghai, China), at 2 Hz frequency and 0.5 ms pulse width for 30 minutes. EX-LE5 will be connected to ST35, and SP10 will be connected to ST34 with a pair of electrodes [10,13]. Different stimulation intensities will be allocated to the strong EA and weak EA groups. The strong EA group will receive the maximum tolerable intensity of current (2 mA < current < 5 mA). However, patients in the weak EA group will receive low-intensity current (0 mA < current < 0.5 mA), and they will be instructed to ask the doctor to stop the increase in intensity when the sensations of current occur. After the intervention period, all needles and the EA apparatus will be removed (Table 1).

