### Outcome assessments

#### Primary outcome measurements

The primary outcome measurements are the Visual Analog Scale (VAS), DNIC function and the Western Ontario and McMaster Universities Osteoarthritis Index (WOMAC).

VAS is an internationally recognized pain scale. It is a 100-mm line ranging from 0 (no pain) to 100 (pain as bad as it could be) [14].

The prediction of chronification of acute pain can be indicated by DNIC function, which means that pain elicited by a noxious stimulus applied to a given body site can be attenuated by application of a conditioning noxious stimulation to another, even distant body region [15]. DNIC function will be measured according to the procedure shown in Figure 3. On the Ashi-point (pain spot) of the affected knee, the research assistant will apply a 180-g von Frey filament (bending it so that it forms a 45-degrees angle with the skin) three to five times within a 1-cm-diameter circle (Figure 3A). The patients will be asked to rate the intensity of pain as VAS1 [5], which is the induced mechanical pain score of the affected knee. Then, the patients will be asked to immerse the contralateral hand, including the wrist, into nociceptive cold water (10 to 12°C) for 1 minute and rate the intensity of the pain induced by the 180-g von Frey filament on the Ashi-point as VAS2 (Figure 3B). For healthy people, the conditioning cold noxious stimulation can activate the descending inhibitory system of the spinal cord. VAS2 is used to detect the induced mechanical pain score of the affected knee after conditioning with the cold noxious stimulation on the contralateral hand. Finally, DNIC function will be assessed by measuring the difference in pain ratings before and after immersion (DNIC = (VAS1-VAS2)/VAS1). Thus, the decreased ratio in pain scores of the affected knee before and after the cold noxious stimulation of the hand is the DNIC function [2,16].

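### The Figure 3 legend has doctors rate VAS2 while the text has the patient rate it, so DNIC as the legend describes it is a difference between two raters

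*Protocol article*

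**What the plan says.** The Protocol article describes the DNIC measurement twice.

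- **Primary outcome measurements (text).** A research assistant applies the filament at the painful spot on the knee. For the first score, "The patients will be asked to rate the intensity of pain as VAS1". The patients then put the opposite hand in cold water and, still as the subject of the sentence, "rate the intensity of the pain induced by the 180-g von Frey filament on the Ashi-point as VAS2". The same paragraph points elsewhere for the method: "DNIC function will be measured according to the procedure shown in Figure 3".
- **Figure 3 legend.** Part A agrees with the text that the patient rates VAS1. Part B changes the subject: "the doctors will rate the intensity of the 180-g von Frey filament-induced pain at the Ashi-point as VAS2".

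Both places give the same formula, "DNIC = (VAS1-VAS2)/VAS1". DNIC is one of three primary outcomes, and the Sample size section rests on it alone. Randomization and blinding states that patients and outcome evaluators are blind, and that "the blind method is not used by acupuncturists in the implementation of EA manipulation".

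**The concern.** DNIC is meant to capture how far one person's felt pain falls after a painful stimulus elsewhere on the body. The subtraction has that meaning only if the same person gives both ratings. If a doctor supplies VAS2, the score mixes the patient's pain inhibition with the gap between how a patient and an observer place the same stimulus on a 100 mm line. This holds even if every doctor is blind to allocation.

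The legend cannot be set aside as decoration, because the text names Figure 3 as the procedure. Staff could follow either version in good faith. The trial is recruiting, and a VAS2 taken from the wrong person cannot be recovered later.

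**Working it through.** No sample size, power or alpha figure depends on this point, so there is no stated figure to reproduce. The check is a comparison of the two descriptions, followed by an illustration of scale.

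**Step 1. Who rates what**

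| Item | Text, Primary outcome measurements | Figure 3 legend |
|---|---|---|
| Rater of VAS1 | patient | patient |
| Rater of VAS2 | patient | doctors |
| Formula | (VAS1 − VAS2)/VAS1 | (VAS1 − VAS2)/VAS1 |
| Raters in the score | one | two |

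The two agree on everything except the rater of VAS2. Both statements are in the current text.

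**Step 2. What a second rater does to the score**

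Let the doctor's VAS2 equal the patient's VAS2 plus an offset d, in mm. Then

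DNIC (legend) = (VAS1 − VAS2 − d)/VAS1 = DNIC (text) − d/VAS1.

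A doctor who rates higher than the patient lowers DNIC by d/VAS1; one who rates lower raises it by the same amount.

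**Step 3. Scale, with assumed inputs**

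The documents give neither a typical VAS1 nor a typical offset, so both are assumptions. For d = 5 mm:

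- VAS1 = 30 mm: 5/30 = 0.167, about 17 points
- VAS1 = 50 mm: 5/50 = 0.10, 10 points
- VAS1 = 80 mm: 5/80 = 0.0625, about 6 points

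The Sample size section assumes DNIC increases of 30% (strong EA), 20% (weak) and 15% (sham). If these are points on the DNIC ratio scale, which the article does not state, the strong–weak gap is 30 − 20 = 10 points. The offset that moves one patient's DNIC by that much is 0.10 × VAS1: 3 mm at 30, 5 mm at 50 and 8 mm at 80.

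**Step 4. What reaches the comparison between arms**

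The shift in an arm's mean DNIC is the average of d/VAS1 in that arm. If d and the spread of VAS1 are alike in the arms, the shifts cancel in the difference. Cancellation is not exact, because d is divided by VAS1. With d = 5 mm everywhere but VAS1 of 40 mm in one arm and 50 mm in another, what remains is 5/40 − 5/50 = 0.125 − 0.10 = 0.025, or 2.5 points. If d itself differs by arm, that difference passes into the comparison: a 5 mm difference in d between strong and weak EA at VAS1 = 50 mm gives 10 points.

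**Step 5. Are the doctors blinded?**

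Randomization and blinding names acupuncturists as unblinded and outcome evaluators as blinded. It does not place the doctors of Figure 3 in either group, so the question stays open.

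**The case against.** The strongest reply is that the legend is a slip for doctors writing down the patient's answer. The text is the fuller account: it names who applies the filament and has the patient give both ratings. The WOMAC description shows doctors in just such a supporting role: "Doctors need to help patients perform the self-assessment, collect the total score from the 24 questions and record it". Education of practitioners also says that outcome assessment methods and form recording will be standardised across the six centres. This reply has weight. The benign reading may be what was meant, and standardisation makes it less likely that sites diverge. But it requires replacing the legend's verb, and the text itself defers to Figure 3. Standardising sites does not help if the procedure they are trained on is the legend.

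Three stronger readings are tempting and are not supported.

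- **That an unblinded practitioner rates VAS2.** A reader might infer this because, in the weak EA arm, patients are treated so that "they will be instructed to ask the doctor to stop the increase in intensity when the sensations of current occur", and the person adjusting the current knows the intensity. But the article uses the word doctor loosely, generally calls the treating staff acupuncturists, and states that outcome evaluators are blind. Nothing identifies the doctors of Figure 3 as those giving treatment. A conflict with the blinding statement is possible, not shown.
- **That WOMAC has the same fault.** It remains the patient's self-assessment, with doctors helping and recording, and this contradicts no other part of the article.
- **That the error could account for the whole assumed strong–weak difference.** That needs an offset that differs by arm, and the documents give no evidence of one.

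**Conclusion.** The instruction for VAS2 is wrong as written. Two descriptions of a primary outcome, one of which refers to the other as the procedure, name different raters. Taken literally, the legend's version is not a valid within-patient change in felt pain, and this conclusion needs no assumption about blinding.

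The size of any effect on the results cannot be derived from the documents. The range of about 6 to 17 points for a 5 mm offset rests on assumed VAS1 values of 80 to 30 mm and describes the shift in an individual score, not the bias in a treatment comparison. Comparison with the planned 10-point gap also assumes that the sample size percentages are points on the DNIC ratio. Bias between arms would arise mainly if the offset differed by arm. Mixed practice across sites would mainly add noise.

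**What to change.** - Correct part B of the Figure 3 legend, and the site procedure if it carries the same wording, so that the patient gives both VAS1 and VAS2.
- State that the blinded evaluators already provided for under Randomization and blinding record these ratings and do not make them.
- Send a short notice to the six sites and ask each who has been giving VAS2 so far.
- If any VAS2 values prove to have been rated by a doctor, flag them and repeat the DNIC analysis without them. If none have, no extra analysis is needed.

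The cost is a wording correction and one message to the sites. The plan already provides for blinded evaluators, so no new staff are needed, and the formula and sample size do not change.

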#### Secondary outcome measurements

The secondary outcome measurements are Numerical Rating Scale (NRS), Emotional Scale (ES), Present Pain Intensity (PPI) and range of motion (ROM).

The NRS of pain is a scale containing the numbers from 1 to 10 on a straight line to measure the magnitude or intensity of pain [18]. It has been shown to have a good predictive validity and has been used to measure the effect of EA on the pain of KOA [12]. All subjects participating in the study will be asked to select a number from 1 to 10 with the nearest 0.5 interval, to represent their maximal OA-induced knee pain in the most recent 2 to 3 days.

Pain, whether acute or chronic, can affect a patient’s emotions. Under normal circumstances, emotion can be distinguished according to four levels, measured as ES: Excellent (0 to 2, face is peaceful, and the patient responds freely), Good (3 to 5, face remains indifferent, and the patient responds to instruction), General (5 to 8, anxiety or depression apparent, face shows some pain, and patient barely answers), and Poor (8 to 10, face clearly shows pain, with moaning and forced posture, and patient fails to answer).

PPI is also one of the clinical tools most commonly used to help patients express the intensity of pain. It moves from 0 to 5, indicating the following levels of pain according to number: no pain, mild discomfort, discomfort, terrible pain and extreme pain.

ROM indicates the maximum range of joint activities. Determination of ROM is a basic step in assessing muscle, bone and neurological damage. It is one of the indicators used to evaluate the scope of damage and degree of joint movement function, and it can be measured with the help of protractor whose axis is placed on the fibular capitulum, with the fixed arm parallel to the long axis of the femur and with the moving arm parallel to the long axis of the fibula while in a prone position. The normal range of motion of the knee is ‘0 to 135°’.

### Sample size

According to a previous study and our pilot data, the sample size calculation assumed an average DNIC increase percentage of 30% for the strong EA group [19]. The DNIC increase percentage for the weak EA group and sham EA group are assumed to be 20% and 15%, respectively. It is assumed that 15% of the trial patients will be lost to attrition. With this scenario, 150 patients need to be allocated to each treatment group to establish a difference among the treatments at a 5% level and with a power of 90% [20].

### Data analysis

Data with normal distribution will be presented as means ± SEM. We will use a one-way analysis of variance (ANOVA) or a two-way ANOVA to determine the overall effect of EA. The Post hoc test (Newman Keuls test) will then be used to determine the statistical differences among individual groups. A *P* value of less than 0.05 will be considered statistically significant. Data showing an abnormal distribution will be analyzed by the Wilcoxon signed-rank test.

In order to determine which EA intervention is the best for each of the different stages of KOA, patients in the three EA groups will be further divided according to four different stages of KOA:The acute pain stage group. The pain of KOA has been ongoing for less than 6 months.The early chronic pain stage group. The pain of KOA has been ongoing for 6 months to 3 years.The medium-term chronic pain stage group. The pain of KOA has been ongoing for 3 to 5 years.The advanced chronic pain stage group. The pain of KOA has been ongoing for more than 5 years (Figure 4A).

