### Design

A randomized, controlled, three-arm, large-scale trial to compare two true EA groups (strong EA and weak EA) with a sham EA group will be undertaken in this study [8]. Four hundred and fifty KOA patients will be recruited from the following six hospitals: the Combined Traditional Chinese and Western Medicine Hospital Affiliated to Huazhong University of Science and Technology, The Third Hospital of Wuhan, Central Hospital of Wuhan, Union Hospital Affiliated to Tongji Medical College of Huazhong University of Science and Technology, Wuhan Hospital of Traditional Chinese Medicine, and The Fifth Hospital of Wuhan. Patients will be randomized in a ratio of 1:1:1 to the strong EA group, weak EA group and sham EA group. After submitting informed consent and being randomized, patients will receive 10 sessions of EA treatment over a period of 2 weeks, with a treatment frequency of 5 sessions per week. Each session will last 30 minutes. Patients will be asked to accept assessments at baseline, as well as at the end of the first and second weeks of the treatment phase. Time points and groups are shown in Figure 1.

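### The planned one-way or two-way ANOVA has no term for baseline, randomisation strata or repeated visits, so it gives up precision that the trial's own data could supply

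*Protocol article*

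**What the plan says.** The Data analysis section fixes the test of treatment: "We will use a one-way analysis of variance (ANOVA) or a two-way ANOVA to determine the overall effect of EA". It continues: "The Post hoc test (Newman Keuls test) will then be used to determine the statistical differences among individual groups", with a P "value of less than 0.05 will be considered statistically significant". No covariate, stratum or within-patient term is named. Nor does it say which visit is analysed, or what the second factor of a two-way model would be. The same section then divides patients into four stages by duration of pain.

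Two other sections describe design features that this model does not use:

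- Design: "Patients will be asked to accept assessments at baseline, as well as at the end of the first and second weeks" of treatment. That makes one pre-treatment and two post-treatment assessments, and no outcome is exempted.
- Randomization and blinding: patients are allocated "through the stratified block randomization method of SAS version 9.1.3". The stratification factor is not named. The Design section lists six recruiting hospitals but does not say that hospital is the stratum.

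**The concern.** The trial collects a baseline value, two follow-up values and stratum membership for each patient, and the named analysis uses none of these to sharpen the comparison of arms. Three separate matters are involved, and they do not act in the same direction.

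- **Baseline.** Leaving it out keeps between-patient variation in the error term and leaves chance baseline imbalance in the estimate. This costs power.
- **Strata.** Stratifying the randomisation and then omitting the strata gives standard errors that are too large for the design.
- **Visits.** With one-way and two-way models both open, it is unclear whether a patient contributes one value or several. If several were entered as though from different patients, the P value for arm could be too small.

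Precision matters most for strong versus weak EA. The Abstract and the Discussion both present this as a question that the trial will answer, and the assumed gap there is smaller than for strong versus sham.

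**Working it through.** **Inputs from the protocol article.** Sample size section: average DNIC increases of 30%, 20% and 15% (strong, weak, sham), 150 per arm, 15% attrition, 5% level, 90% power. Design section: baseline plus two follow-up visits.

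**Inputs assumed.** The article gives no SD and no correlation between visits. Correlations ρ of 0.3, 0.5 and 0.7 are used throughout.

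**1. The plan's own figure.** Without an SD, 150 per arm cannot be recomputed as a comparison of means. It can only be turned round to find the SD that would justify it.
- Evaluable per arm: 150 × 0.85 = 127.5.
- Mean of the three effects: (0.30 + 0.20 + 0.15)/3 = 0.2167. Sum of squared deviations: 0.0833² + 0.0167² + 0.0667² = 0.01167.
- A three-group F test at 5% with 90% power needs noncentrality of about 12.75.
- SD = √(127.5 × 0.01167/12.75) ≈ 0.34.

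**2. Precision gained from baseline.** Assuming equal variances at baseline and follow-up:
- ANCOVA variance relative to post-score ANOVA = 1 − ρ².
- Change-score variance relative to post-score = 2(1 − ρ), so ANCOVA relative to change-score = (1 − ρ²)/[2(1 − ρ)] = (1 + ρ)/2.

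| ρ | ANCOVA / post-score | Reduction | ANCOVA / change-score | Reduction |
|---|---|---|---|---|
| 0.3 | 0.91 | 9% | 0.65 | 35% |
| 0.5 | 0.75 | 25% | 0.75 | 25% |
| 0.7 | 0.51 | 49% | 0.85 | 15% |

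**3. Strong-versus-weak power at the back-solved SD.**
- Standardised difference: 0.10/0.3415 = 0.293.
- Unadjusted: 0.293 × √(127.5/2) = 2.34, and Φ(2.34 − 1.96) ≈ 65%.
- ANCOVA at ρ = 0.5: 0.293/√0.75 = 0.338, then 0.338 × √(127.5/2) = 2.70, and Φ(2.70 − 1.96) ≈ 77%.
- At ρ = 0.5 the two ratios in step 2 coincide, so this gain does not depend on whether post or change scores would have been analysed.

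**4. Omitting the strata.** Null simulations assumed six strata, 126 patients per arm, ρ = 0.5 and 3,000 runs. One-way ANOVA without strata or baseline rejected 3.7% of the time when strata carried 10% of the variance, and 3.0% when they carried 20%. With strata and baseline in the model, the rates were 4.7% and 5.6%. Omission is therefore conservative.

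**5. Visits entered as independent.** With k equally correlated visits, the arm mean square is inflated by 1 + (k − 1)ρ while the pooled error term is not. In large samples, type I error for the arm main effect is P(χ²₂ > 5.99/[1 + (k − 1)ρ]).

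| ρ | k = 2 | k = 3 |
|---|---|---|
| 0.3 | 10.0% | 15.4% |
| 0.5 | 13.6% | 22.4% |
| 0.7 | 17.2% | 28.7% |

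Simulation (128 per arm, 8,000 runs) at ρ = 0.5 gave 13.9% and 22.5%. In the same simulations, one value per patient (the last visit or the patient's mean) gave 4.9% to 5.4%.

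**The case against.** A reader might infer that the written plan carries a type I error of 14% to 23%. The article does not support that. Those values need visit as the second factor, visits handled as separate patients, the arm main effect as the test, and a correlation near 0.5. The article states none of these. The only second grouping in its Data analysis section is disease stage, and an arm-by-stage ANOVA with one value per patient does not inflate error. The chart that may show the layout was not available for this review. The three-visit figure also counts baseline as one of the visits. In that layout the natural test of treatment is arm-by-visit, where the same mistake errs the other way: at ρ = 0.5 the rejection rate is P(χ²₄ > 9.49/0.5), about 0.1%. All of this stands, so the inflation can only be stated as conditional.

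Baseline may not be wholly ignored either. The sample size is framed as an increase in DNIC, which suggests a change score. That also stands, but it does not remove the loss, because ANCOVA has lower variance than change-score ANOVA at every correlation below 1.

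Hospital as the stratum and an SD of 0.34 are inferences, not statements of the article. They are marked as such here, and the fix does not depend on either.

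The last objection is that covariates and covariance structure usually belong in a statistical analysis plan, which is not shown. Silence alone would be no finding. Here, however, the article names a specific method, and that method does not match the design described elsewhere in the same article. Reporting SEM rather than SD is a matter of presentation, and nothing here rests on it.

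**Conclusion.** The point holds as a free improvement. The named ANOVA is not invalid on its most natural readings, but it is less precise than the design allows on each of them. The loss is 9% to 49% of variance against post-score analysis and 35% to 15% against change-score analysis, for assumed ρ of 0.3 to 0.7. The rise in strong-versus-weak power from about 65% to 77% rests on two assumptions: the back-solved SD of about 0.34 and ρ = 0.5.

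Omitting baseline does not inflate type I error under randomisation, and omitting strata lowers it. Only one reading would inflate it, namely visits entered as independent observations and judged on the arm main effect. Error would then be about 10% to 17% with two visits or 15% to 29% with three, over the same range of ρ. The article leaves that reading open but does not adopt it.

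**What to change.** Replace the choice of one-way or two-way ANOVA with one pre-specified model, either:

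- an ANCOVA of the week-2 value on arm; or
- a linear mixed model of the week-1 and week-2 values with arm, visit and arm-by-visit, unstructured within-patient covariance, and the week-2 arm contrast as primary.

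In either model, adjust for the baseline value of the outcome and for whatever factors were used to stratify randomisation, and name those factors. Report between-arm differences with 95% confidence intervals. If a two-way model is kept for disease stage, say so and state that each patient contributes one value.

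The cost is a paragraph of text and no extra patients, visits or measurements. One matter needs care. DNIC is a ratio with the first pain rating as its denominator, and the article itself anticipates non-normal data. The model's residuals should therefore be checked, with a pre-stated alternative if they are poor.

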## Background

Knee osteoarthritis (KOA) is one of the most common types of osteoarthritis and often occurs in older adults [1]. Patients with KOA often suffer from pain around the joints and have a high risk of chronification of acute pain. Chronification of acute pain means that persistent acute pain without positive intervention can damage the nervous system and then change into intractable chronic pain [2]. In recent years, a series of clinical randomized controlled trials indicated that electroacupuncture (EA) is effective for treating various painful diseases such as KOA in the acute phase but did not solve the clinical problems of the chronification of acute pain of KOA [3].

The concept of diffuse noxious inhibitory controls (DNIC) has attracted particular attention in the past decades, which means under normal conditions, pain can be attenuated by a conditioning noxious stimulus to a remote body region [4]. DNIC function is now regarded as a reliable indicator for predicting the risk of chronic pain [5,6]. DNIC function in KOA patients has been shown to gradually decrease with the development of chronic pain [7]. Thus, we hypothesized that the process of chronification of acute pain may be related to gradually impaired DNIC function, and EA may prevent the occurrence of chronification of acute pain by improving DNIC function.

The aim of this study is to explore whether EA can reverse impaired DNIC function by reducing the pain of KOA during the process of chronification of acute pain. Moreover, we will screen for the best EA therapeutic regimen, which will include optimizing the intensity of the current used in the EA stimulation and determining the best stage for effective EA intervention using a randomized controlled clinical trial.

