**Figure 4 Fig4:**
[figure not shown]
**Data analysis chart. A**. We will divide the three electroacupuncture (EA) groups into four different stages to screen separately for the stage where the EA intervention will be most effective. **B**. We will divide all patients into four stages and compare the effects of strong, weak and sham EA separately within the different stages. The Visual Analog Scale (VAS), diffuse noxious inhibitory control (DNIC) function, Western Ontario and McMaster Universities Osteoarthritis index (WOMAC), Numerical Rating Scale (NRS), Emotional Scale (ES), Present Pain Intensity (PPI), range of motion (ROM) will be measured by the procedure outlined in the chart.

The effect of EA on the different stages of KOA will be observed, and the stage with the best response to EA intervention will be discussed. Furthermore, in yet another comparison, we will divide all patients into the four stages and then compare the effects of the strong, weak and sham EA groups within the different stages separately (Figure 4B).

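### Newman-Keuls does not hold 5% once more than three means are compared, and the arm comparisons within the four stages carry no adjustment across stages

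*Protocol article*

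**What the plan says.** The Data analysis section starts with an overall test: "We will use a one-way analysis of variance (ANOVA) or a two-way ANOVA to determine the overall effect of EA". It continues: "The Post hoc test (Newman Keuls test) will then be used to determine the statistical differences among individual groups". The significance threshold is P < 0.05. The factors of the two-way ANOVA are not named.

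Two stage analyses follow. In the first, "patients in the three EA groups will be further divided according to four different stages of KOA", and the legend to Figure 4A explains that this is done separately in each arm to find the stage with the best response. In the second, the Figure 4B legend says: "We will divide all patients into four stages and compare the effects of strong, weak and sham EA separately within the different stages". The section states no adjustment across stages.

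**The concern.** Newman-Keuls takes the critical value for each step from the studentized range of only the means still in that step. With up to three means this protects the 5% level. With four or more, two or more separate blocks of equal means can exist, and each block is then tested at its own 5%.

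The article names this test and also plans comparisons of four means, and possibly more. It expects stages to differ: the Background says "DNIC function in KOA patients has been shown to gradually decrease with the development of chronic pain", and the Discussion expects early stages to respond better than late ones. Partly equal, partly different stage means are therefore a realistic case. At stake are the stage-level claims, namely which stage responds best and which intensity works best in which stage. The main three-arm comparison is not at stake.

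**Working it through.** **Inputs.** Three arms at 1:1:1, 150 per arm, 15% attrition, four stages and alpha 0.05, all from the article. Evaluable patients per arm: 150 x 0.85 = 127.5. Per arm and stage: 127.5 / 4 = about 32. The even split over stages is an assumption, since the article gives no stage distribution. The article states no familywise error rate for its post hoc tests, so the only figure to check against is the 5% level. All rates below are for one outcome at one visit.

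**1. Three arms, one-way.** Simulated Newman-Keuls error, 127 per arm: 5.0% with all arms equal and 5.1% with one arm different. The level holds.

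**2. Four stages within one arm (Figure 4A).** With four means, only one pattern allows more than one block of equal means: two separated pairs. The limit is then 1 - 0.95^2 = 9.75%. All four equal, three equal plus one different, or a single equal pair leaves one block, at no more than 5%. Simulation with 32 per stage and two equal pairs:

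| Gap | Newman-Keuls |
|---|---|
| 0.5 SD | 7.9% |
| 1 SD | 9.8% |
| 2 SD | 9.9% |

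Tukey critical values give about 2% in the same setting. These errors are false stage differences, counted per arm.

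**3. All 12 arm-by-stage cells in one Newman-Keuls family (an assumption).** Arms equal within each stage, 32 per cell, chance of at least one false within-stage arm difference:

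| Gap between adjacent stages | No preceding F test | Overall 12-cell F test required |
|---|---|---|
| 0 | 1.4% | 1.1% |
| 0.25 SD | 4.7% | 4.6% |
| 0.5 SD | 12.1% | 11.4% |
| 0.75 SD | not run | 17.9% |
| 1 SD | 18.2% | 17.8% |
| 2 SD | 18.6% | not run |

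The limit for four blocks is 1 - 0.95^4 = 18.5%. Tukey on the 12 cells gives about 1%.

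**4. The same 12 cells, with post hoc tests only after a significant EA effect.**
- No arm effect, 1 SD stage gaps: 3.1% if the arm F test is the gate, and 6.9% if either the arm or the interaction F test opens it.
- Strong EA truly better by 0.4 SD (assumed), weak equal to sham, arm F gate: 2.4%, 7.0%, 10.6% and 13.8% at stage gaps of 0.25, 0.5, 0.75 and 1 SD.
- Strong EA different by 0.5 or 1 SD, weak equal to sham, stages 3 SD apart, arm F gate: 16.1% and 18.0%.

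In the last two settings the false claim is weak versus sham.

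**5. Three arms compared separately in each of four stages (Figure 4B).** Each family has three means, so each holds 5%. Across four independent stages with no arm effect in any: 1 - 0.95^4 = 18.5%. Simulated: 19.4% with Newman-Keuls and 18.8% with Tukey. The post hoc test makes no material difference. Holm across all 12 contrasts brings the rate to about 5%.

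**The case against.** A reader might infer that Newman-Keuls makes this trial declare false arm differences about 18% of the time. The article does not support that, for four reasons.

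- **Family.** It neither names the second ANOVA factor nor says that all 12 cells enter one family. If the arm marginal means are compared, the rate is 5%.
- **Gate.** The ANOVA is there to establish the overall effect of EA, and the post hoc test follows it. Read that way, with no arm effect, the rate is about 3-7% even at 1 SD stage gaps.
- **Stage gaps.** Gaps of 0.75 SD between adjacent stages mean 3 x 0.75 = 2.25 SD from first to last. The article gives no SD. The assumed 30/20/15 with 127 evaluable per arm and 90% power in a three-group ANOVA would imply about 34 points, so 2.25 x 34.1 = about 77 points, against a planned strong-sham difference of 30 - 15 = 15. The Background also speaks of DNIC level, whereas the sample size concerns DNIC increase.
- **Figure 4B.** Its families have three means each, so its 18.5% cannot be blamed on Newman-Keuls.

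All four stand against the strong reading. A further inference, about 14% for nine arm-by-visit cells (1 - 0.95^3 = 14.3%), treats repeated measurements on the same patients as independent and is not relied on here.

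It can also be said that a condensed article leaves factors and contrasts to the full plan, and that the stage work is screening. The first explains the unnamed factors but not the choice of test, which the article fixes. The second softens the consequence, yet the Discussion lists early versus late stage among the questions the trial should answer. Neither removes the four-mean problem in Figure 4A, which needs no assumption about the two-way model.

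**Conclusion.** The concern holds in a limited form and should be corrected.

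- **Stages within an arm (Figure 4A):** the named test can give about 8-10% false stage differences per arm instead of 5%. This requires two separated pairs of equal stages with a gap of 0.5 SD or more; the simulated figures assume about 32 patients per stage.
- **All 12 cells as one family:** about 18% is a worst case that depends on an unstated family, stage gaps of 0.75 SD or more and how the post hoc tests are gated. At 0.25 SD it is about 5%.
- **Arms within stages (Figure 4B):** about 18.5% across the four stages if no arm effect exists in any. The cause is the missing adjustment across stages.
- **Plain three-arm comparison:** sound, and can stay as written.

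**What to change.** Keep Newman-Keuls for the plain three-arm comparison, and add one sentence to Data analysis covering the two stage analyses.

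- **Stages within each arm:** replace Newman-Keuls with Tukey-Kramer, or apply Holm over the six stage pairs. This holds 5% in each arm, matching the separate analysis by arm in Figure 4A.
- **Arms by stage:** take the 3 pairs x 4 stages = 12 within-stage contrasts from the two-way arm-by-stage model and apply Holm across all 12. Switching to Tukey inside each stage alone would change nothing. This also settles which factors and contrasts the two-way analysis uses.

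The change needs no new data or patients. It costs some power for individual stage-level comparisons: the first Holm step over 12 contrasts uses 0.05 / 12 = 0.0042, so |z| of about 2.87, against 1.96 for an unadjusted contrast.
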